### Statistical Analysis

Demographic and baseline characteristics of the participants will be reported as frequencies and percentages for categorical variables and means and standard deviation or median and interquartile range for continuous variables, as appropriate.

For WP 1, descriptive statistics will be reported for the results. For WP 2, a severity variable will be constructed that will include mortality and hospitalization, in addition to the presence of pneumonia in cases of COVID-19. Quantitative variables will be described as means and standard deviation, while categorical variables will be described as the proportion of exposed and unexposed individuals. Univariate tests will include the Student *t* test and the chi-square test, as appropriate. For the primary outcome, marginal structural models will be fitted to estimate causal effects by correcting for confounders. Inverse probability weights will be estimated as a function of propensity score using sociodemographic variables and clinical variables. The inverse probability weights will be used in the marginal structural model to estimate the risk ratio and confidence intervals for the prevalence of each outcome among individuals exposed to antibiotics versus those not exposed to antimicrobials. During the assessment of the correlation of prior antibiotic exposure with the different outcomes, patients will only be counted once and assigned to the worst outcome (with the severity of COVID-19 ranked in decreasing order as death, hospitalization, and pneumonia). The Wald test will be used to determine whether the adjusted risk ratios are significantly different from zero at a significance level of 5%.

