## Introduction

It is estimated that 10 million people could die worldwide by 2050 from infections caused by multidrug-resistant pathogens if urgent measures are not taken to combat the problem of antimicrobial resistance, mainly among gram-negative bacteria and especially enterobacteria [1]. Antibiotic resistance is an individual health and public health problem; increasing community resistance can prolong the infectious process, increase the risk of infecting other individuals, and in the long term, lead to increased costs. Inappropriate use of antibiotics increases the frequency of related and sometimes serious side effects and causes increased mortality [2,3]. Unnecessary use of antimicrobials is the most important cause of resistance generation in the community, and it is estimated that 80% of antimicrobials are prescribed in primary health care (PHC) [4].

Urinary tract infections (UTIs) are a common infection in PHC, and most patients are treated with antibiotics [5-7]. In Spain, UTIs represent the second most frequent cause of antibiotic prescriptions [8]. Almost 60% of women experience at least one episode during their lifetime [9,10]. Antibiotic treatment of uncomplicated UTIs is, in most cases, empirical, and the selection of the antimicrobial is made according to the most frequently involved pathogen and local resistance. Several studies have suggested that up to 50% of antibiotic prescriptions are inappropriate [11-13]. There is a tendency to use broad-spectrum antibiotics, which do not usually provide substantial improvements in efficacy over narrower-spectrum antibiotics and instead favor increased resistance [4].

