### Study End Points

#### Primary End Points

The primary end points of the first phase for WP 1 are the proportion of different types of UTI (uncomplicated UTIs, recurrent UTIs, and pyelonephritis), the percentage of first-line antibiotics used for different types of UTI according to the national guidelines [40,41], and the percentage of inappropriate prescriptions, with the type of antibiotic of these prescriptions. The primary end points for WP 2 are the percentage hospitalization rate and the proportion of UTIs with complications (ie, pyelonephritis, sepsis, pneumonia, and COVID-19). COVID-19 infection will be determined by ICD-10 codes, tests (ie, polymerase chain reaction tests, rapid antigen tests, and others), or both.

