#### Secondary End Points

The secondary study endpoints are (1) types of UTI in women aged ≥18 years with the percentage of recurrent UTIs (defined as more than 2 UTIs in the last 6 months or more than 3 episodes in the last year); (2) types of UTI in men aged ≥18 years; (3) the percentage of urine cultures and laboratory tests ordered for the different types of UTI in both men and women; (4) the percentages of different types of antibiotics used in patients with UTIs, as well as dosage and duration of treatment; (5) the percentage of women with recurrent UTIs who were treated with suppressive therapy (ie, antibiotic treatment 3 times a week for 6 months or more) and the duration of the therapy; (6) the percentage of infectious complications, especially acute pyelonephritis and sepsis, in the 2 cohorts (ie, women with recurrent UTIs with suppressive therapy and women with recurrent UTIs without suppressive therapy but with UTIs treated punctually; (7) the percentage of pneumonia and COVID-19 infection in the 2 cohorts (ie, women with multiple antibiotic regimens for UTIs or suppressive therapy and women with UTIs treated punctually); and (8) the frequency of clinical variables of people affected by UTI who progress to acute pyelonephritis.

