## Discussion

We expect to find inadequate management in a high percentage of UTI cases, considering that on many occasions patients are treated with second- or third-line antibiotic therapies with a preference for the longest regimens. Likewise, the use of suppressive antibiotic therapy as a prophylaxis in cases of recurrent UTI is expected to vary in our study.

In addition, we aim to determine whether women with recurrent UTIs treated with antibiotic suppressive therapy have a higher incidence and severity of potentially serious future infections, with special attention to acute pyelonephritis, urosepsis, COVID-19, and pneumonia, in comparison to women who are treated with antibiotics only when they present with a UTI.

All the information obtained in this first phase will allow us to continue with the following WPs of the project. Furthermore, if we find the inappropriate use of antibiotics, we will work on the creation of proposals to promote the correct treatment of UTIs in our environment according to clinical guidelines [40,41]. In this way, we will promote responsible management of UTIs in PHC among health care personnel and patients. In addition, our study will provide valuable information for health care policy makers and national programs to optimize the use of antimicrobials.

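### The only adjusted WP 2 model contrasts antibiotic exposure with no exposure, but both WP 2 cohorts receive antibiotics, so the stated comparison has no adjusted model

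*Protocol article*

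**What the plan says.** In Statistical Analysis, the adjusted comparison for WP 2 is introduced as follows: "For the primary outcome, marginal structural models will be fitted to estimate causal effects by correcting for confounders". Its inverse probability weights are then used to estimate the "risk ratio and confidence intervals for the prevalence of each outcome among individuals exposed to antibiotics versus those not exposed to antimicrobials". The next step is worded in the same terms: "During the assessment of the correlation of prior antibiotic exposure with the different outcomes". The section does not mention suppressive therapy, the two cohorts, or an amount or type of antibiotic.

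The cohorts are set out under Secondary End Points. End point 6 (infectious complications, especially pyelonephritis and sepsis) compares "women with recurrent UTIs with suppressive therapy and women with recurrent UTIs without suppressive therapy but with UTIs treated punctually". End point 7 (pneumonia and COVID-19) puts multiple antibiotic regimens or suppressive therapy on one side and UTIs treated punctually on the other. End point 5 defines suppressive therapy as a long-term antibiotic regimen.

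The Discussion states the aim as suppressive therapy "in comparison to women who are treated with antibiotics only when they present with a UTI", and the Conclusions of the Abstract say the same in substance. The Objective in the Abstract also refers to two cohorts of women, and to which antibiotics they took and how much in total.

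Under Primary End Points: "The primary end points for WP 2 are the percentage hospitalization rate and the proportion of UTIs with complications". The complications listed there are pyelonephritis, sepsis, pneumonia and COVID-19.

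**The concern.** The article describes one confounder-adjusted model, and its contrast does not match the cohorts that WP 2 compares. An analyst who follows the text as written obtains either a model with no reference group or a risk ratio for another question. That risk ratio could then be reported as evidence on suppressive therapy, which it would not be. The comparison of interest would be left with the unadjusted t and chi-square tests, the only other comparative methods specified. Women put on suppressive therapy are likely to differ from those treated per episode, and the Discussion itself names confounding as a limitation, so unadjusted tests are a weak basis for this question.

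**Working it through.** The article states no figure that depends on this contrast, so there is nothing to reproduce. The check sets the definitions side by side.

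**1. Who is exposed under the written contrast.** Let A = 1 for a woman exposed to antibiotics and A = 0 for one not exposed.

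| Group | Source | A as written |
|---|---|---|
| Suppressive therapy | Secondary end points 5 and 6 | 1, by definition |
| Multiple regimens or suppressive therapy | Secondary end point 7 | 1, by definition |
| UTIs treated punctually | Secondary end points 6 and 7; Discussion | 1, by definition |
| No antibiotic | Not defined as a cohort anywhere | 0 |

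Within the cohorts P(A = 1) = 1 and P(A = 0) = 0. An unexposed person's weight is 1 / P(A = 0 given covariates), which would be 1/0. The reference group is empty and its weights are undefined.

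**2. If the unexposed come from outside the cohorts.** Let S, E and U be the confounder-adjusted risks under suppressive, per-episode and no antibiotic treatment, and p the suppressive share of the exposed arm.

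- The model estimates [pS + (1 − p)E] / U.
- The study question asks for S / E.

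The first does not determine the second. The article gives none of p, S, E or U.

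**3. If exposure means antibiotics within a look-back window.** A woman treated per episode is exposed if her last course falls inside the window and unexposed if it does not. Per-episode women then sit in both arms, and the ratio reflects recency of use. It does not compare the two treatment strategies.

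**4. If exposed is shorthand for suppressive therapy.** The contrast would then be the intended one, but the article nowhere says so, and a reference group described as not exposed to antimicrobials does not fit women treated at each UTI.

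**5. Whether another adjusted model covers the comparison.** WP 1 is descriptive. For WP 2, Statistical Analysis lists univariate tests and the marginal structural model. The Discussion promises sensitivity analyses and other methods where they fit, but ties none of them to this contrast.

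**6. Whether the end points separate the model from the cohorts.** The model is for the primary outcome, whereas the cohort percentages are secondary end points 6 and 7. However, the complications in the WP 2 primary end points are the same four as in end points 6 and 7, and the Objective places the two cohorts in the study aim.

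**7. Whether the two cohort definitions agree.** Take a woman with recurrent UTIs, several per-episode courses and no suppressive therapy. Under end point 6 she is a comparator. Under end point 7 her multiple regimens put her on the other side. The comparator in end point 7 is also not restricted to recurrent UTIs. A single restated contrast cannot serve both end points unchanged.

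**The case against.** The strongest reply is that the exposure is undefined rather than wrong. Statistical Analysis speaks of prior exposure, and its COVID-19 severity ranking resembles the outcome of the earlier COVID-19 study described in the Introduction, which measured antibiotic history over set periods. With a window, some women treated per episode could be unexposed, so the reference arm need not be empty. An exposure window is also a detail that an article may leave to the full protocol. This stands to the extent that the empty reference group follows only from the literal reading. It does not rescue the plan: a window still does not yield suppressive versus per-episode treatment, and the article fixes a contrast that conflicts with its own cohorts, which is more than an omitted detail.

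A second reply is that the Introduction describes the WP 2 aim broadly, as antibiotic use for repeated UTIs and infectious complications, which an exposed-versus-unexposed contrast loosely fits. That is fair for that sentence. But the Objective asks about types and total consumption in two cohorts, which a yes/no exposure does not capture, and both the Abstract's Conclusions and the Discussion state the suppressive-versus-per-episode comparison.

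A third reply is that the planned sensitivity analyses might cover the gap. They might, but none is specified for it.

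A reader might also infer that the unexposed arm is nearly empty in practice, that the weights would be extreme, or that the suppressive effect would be diluted by a calculable amount. The documents do not support this. The statement that "most patients are treated with antibiotics" concerns UTIs in primary care generally and gives no share for recurrent UTIs. A dilution figure would also need the suppressive share and the risk in untreated women relative to those treated per episode, and neither is given.

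**Conclusion.** The point holds as a contradiction between the model and the cohorts. The article specifies a risk ratio "among individuals exposed to antibiotics versus those not exposed to antimicrobials", while the WP 2 question and cohorts compare women who all receive antibiotics. Under the literal reading there is no reference group within the cohorts; under the outside-reference or look-back reading the estimand is a different one. Only an unstated shorthand reading gives the intended contrast. As written, no adjusted model is specified for the stated comparison.

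In scope, this affects the whole adjusted comparison in WP 2. No numerical bias can be attached to it, and the conclusion needs none: it rests only on the definitions in the article and on taking its words at face value. It does not show that the data or the model class are unable to answer the question. With the contrast restated, the same approach can address it.

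**What to change.** - In Statistical Analysis, replace the exposed-versus-unexposed contrast with the cohorts from Secondary End Points, and let the propensity score model cohort membership. For end point 6, that is suppressive therapy among women who meet the recurrent-UTI definition.
- State that this model applies to the WP 2 complications and to hospitalization, so that the primary end points and end points 6 and 7 are covered.
- Reconcile the cohort definitions in end points 6 and 7, or specify a separate contrast and propensity model for each. The end point 6 wording should not simply be carried over to end point 7, because that would contradict end point 7's own cohorts.
- If any antibiotic versus none, or total consumption, is also of interest, make it a separate, labelled analysis with its reference group and exposure window defined.

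The cost is mainly wording in the analysis section, plus a decision on the cohort definitions. The data sources and model class stay the same. Separate contrasts for the two end points would mean fitting one further model.

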**Objective:**

This paper presents the protocol for the first phase of the Urinary Tract Infections in Catalonia (Infeccions del tracte urinari a Catalunya) project. We aim to examine the epidemiology of the different types of UTIs in Catalonia (an autonomous community in Spain) and their diagnostic and therapeutic management by health professionals. Furthermore, we aim to evaluate the correlation between types and total consumption of antibiotics for recurrent UTIs in 2 cohorts of women with the presence and severity of infectious complications of urological origin, especially pyelonephritis and sepsis, and 2 potentially serious infections: pneumonia and COVID-19.

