Another dilemma faced by practitioners is the recommendation to give suppressive antibiotic treatment lasting more than 6 months to women who have repeated UTIs (defined as more than 2 UTIs in the last 6 months or more than 3 in the last year) [26]. However, this practice is not exempt from potential risks. In a recent article, a clear correlation was reported between a history of antibiotic use in the previous 2 years and the severity of COVID-19 (with severity defined as a variable combining death, hospitalization, and the presence of pneumonia), based on data from the Information System for the Development of Research in Primary Care (Sistema d’informació per al desenvolupament de la investigació en atenció primària [SIDIAP]) [27]. This correlation was very strong when antibiotics were taken in the previous 2 months, when there were more than 5 antibiotic regimens in the last 2 years, and when antibiotics were used that are critical and should be reserved for special cases, such as cephalosporins and quinolones. In addition, prudent use of antibiotics is necessary due to the increase in antibiotic resistance [3,28].

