For all the above reasons, we propose the current protocol for the Urinary Tract Infections in Catalonia (Infeccions del tracte urinari a Catalunya [ITUCAT]) study, consisting of 4 work packages (WPs) that will be implemented successively in 3 phases, to evaluate different objectives related to UTIs in the adult population in Catalonia and investigate specific aspects of this condition in this population. The first phase of the project, which is presented in this paper, includes the first 2 WPs. WP 1 will evaluate the management of UTIs in Catalonia, and WP 2 aims to evaluate the correlation of antibiotic use for repeated UTIs with the presence of infectious complications in adult women. Subsequently, we will carry out the second phase with the data obtained from the first phase. At this stage, the aim is to create a scale to predict acute pyelonephritis in patients with UTI by evaluating clinical variables; this will be WP 3. Finally, in the third phase, we will perform WP 4, which aims to determine the degree of inadequacy in requests for urine cultures based on clinical practice guidelines and to establish the basis for a training intervention.

The study described in this paper corresponds to the first phase, which includes WP 1 and WP 2.

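### The adjusted WP 2 estimate contrasts antibiotic-exposed with unexposed people, which matches neither the stated objective (type and amount) nor the two antibiotic-treated cohorts

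*Protocol article*

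**What the plan says.** The Abstract (Objective) of the Protocol article sets out to "evaluate the correlation between types and total consumption of antibiotics for recurrent UTIs in 2 cohorts of women", against the presence and severity of infectious complications. The Introduction states the aim more loosely: "WP 2 aims to evaluate the correlation of antibiotic use for repeated UTIs with the presence of infectious complications in adult women".

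The two cohorts appear in three places.
- Secondary End Points, item 6 (pyelonephritis and sepsis): "women with recurrent UTIs with suppressive therapy and women with recurrent UTIs without suppressive therapy but with UTIs treated punctually".
- Secondary End Points, item 7 (pneumonia and COVID-19): "women with multiple antibiotic regimens for UTIs or suppressive therapy and women with UTIs treated punctually".
- The Discussion compares women on suppressive therapy with the others, "in comparison to women who are treated with antibiotics only when they present with a UTI".

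Statistical Analysis then specifies a marginal structural model with inverse probability weights for the primary outcome. It reports a risk ratio for each outcome "among individuals exposed to antibiotics versus those not exposed to antimicrobials". The other comparisons named for WP 2 are univariate t and chi-square tests.

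**The concern.** The exposure in the model is not the exposure in the question. A yes/no antibiotic variable has no term for class, number of courses, cumulative amount or duration, so it cannot give an adjusted answer about type or total consumption. It does not separate the two cohorts either, because women in both have taken antibiotics. Who the unexposed would be, among women with treated recurrent UTI, is not defined.

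At stake is the adjusted part of WP 2. Women given suppressive therapy may well differ from the others in severity and history, and this is the confounding the weights are meant to handle. If the weights serve a different contrast, the cohort comparison rests on crude percentages. A difference confined to heavy use or to certain classes would be averaged into one overall figure.

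**Working it through.** The plan states no power, event rate or effect size for WP 2, and the roughly 2.5 million UTIs under Sample Size are a database count. There is no figure to reproduce. The check sets the text side by side and adds an illustration with assumed values.

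**Step 1: what is asked and what is estimated.**

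| Place | Exposure or comparison | Adjusted? |
|---|---|---|
| Abstract, Objective | Antibiotic type and total amount, in two cohorts of women with recurrent UTI | – |
| Secondary End Points, item 4 | Types, dosage and duration, as percentages of use; not linked to complications | No |
| Secondary End Points, item 6 | Suppressive versus episodic treatment | None described |
| Secondary End Points, item 7 | Multiple regimens or suppressive therapy versus episodic treatment | None described |
| Discussion | Suppressive therapy versus treatment only at a UTI | None described |
| Statistical Analysis | Exposed versus not exposed | Yes, by weighting |

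The one adjusted row matches none of the others.

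**Step 2: where the cohorts fall.** The article defines recurrence as more than 2 UTIs in 6 months or more than 3 in a year, so at least 3 episodes. If each episode is treated, every such woman has at least 3 courses. Both cohorts are then exposed, and the unexposed group is close to empty within recurrent UTI or must come from another population.

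**Step 3: what the yes/no risk ratio would show (illustration; all values assumed).** Let s be the share of suppressive users among the exposed. Let RRp and RRs be the risk ratios against no treatment for episodic and suppressive treatment, with confounding removed.

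- Yes/no RR = (1 − s) × RRp + s × RRs
- Cohort RR = RRs / RRp

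| s | RRp = 1.0, RRs = 1.5 (cohort RR 1.5) | RRp = 1.0, RRs = 2.0 (cohort RR 2.0) | RRp = 1.2, RRs = 1.8 (cohort RR 1.5) |
|---|---|---|---|
| 5% | 1.025 | 1.05 | 1.23 |
| 10% | 1.05 | 1.10 | 1.26 |
| 20% | 1.10 | 1.20 | 1.32 |
| 40% | 1.20 | 1.40 | 1.44 |

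With RRp = 1.0 and RRs = 2.0 the formula reduces to 1 + s, which gives 1.10, 1.20 and 1.30 at s = 10%, 20% and 30%.

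Two things follow. The same yes/no value of 1.05 arises from a cohort RR of 1.5 (s = 10%) or 2.0 (s = 5%). And one cohort RR of 1.5 goes with yes/no values from 1.025 to 1.44 in this table. The yes/no estimate therefore does not identify the cohort effect. The same mixing argument applies to amount and to class.

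**The case against.** **Detail may sit elsewhere.** The article is condensed. Exposure coding, class groupings and look-back windows often belong in an analysis plan, variables are referred to an appendix, and the Discussion promises unspecified sensitivity analyses. The article also never says that no other exposure will be modelled. This stands as a limit: the point can only be that no other adjusted estimate is described. It does not remove the point, because the article names the contrast, and that contrast conflicts with its own objective.

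**The model is for the primary outcome; the cohorts are secondary.** That is how the text is arranged. But the Objective and the Discussion present the cohort comparison as the WP 2 question, and no adjusted analysis is described for the secondary items.

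**The aim is sometimes looser.** The Introduction's wording on antibiotic use is closer to a yes/no exposure. The Objective and the cohort definitions are more specific, and the model does not fit them.

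A reader might infer two stronger claims, which the document does not support.
- *That WP 2 cannot be answered at all.* Items 6 and 7 still give complication percentages by cohort, item 7 is a coarse split by intensity, and univariate tests are named. An unadjusted answer is planned.
- *That the motivating study found an effect only for many courses or critical classes, so a yes/no exposure could not reproduce it.* The Introduction reports a clear correlation of COVID-19 severity with any antibiotic history in the previous 2 years. It describes the correlation as very strong for use in the previous 2 months, "when there were more than 5 antibiotic regimens in the last 2 years", and for critical classes. The result was stronger in those groups, not exclusive to them.

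**Conclusion.** The concern holds for the adjusted analysis as described. The modelled contrast answers neither the objective on type and total consumption nor the comparison of the two cohorts, because both cohorts are antibiotic-treated. Cohort comparisons remain, but unadjusted; type and amount have no adjusted estimate.

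The mismatch rests on the text alone. Its numerical size cannot be derived from the document. The 1.10 to 1.30 range assumes a doubled risk in heavy users, no excess risk in other exposed women, and heavy-user shares of 10% to 30%. It shows that dilution is possible, not that it is likely. That the unexposed group is nearly empty within recurrent UTI assumes that episodes are treated. The change should be made before the analysis, since it decides what the weighted model estimates.

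**What to change.** Restrict the weighted marginal structural model for WP 2 to women with recurrent UTI, and replace the exposed/not exposed contrast by:

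1. **Suppressive versus episodic treatment** as the main exposure. Items 6 and 7 describe the first cohort differently (item 7 adds multiple regimens), so state which definition the model uses.
2. **Total consumption over a fixed look-back that ends before outcome follow-up starts.** Measure it so that suppressive therapy counts by amount or days, for example dispensed amount from invoice data. A count of courses could record six months or more of suppressive treatment as a single course and rank those women lowest. Set categories from the cohort's own distribution, with a trend test. A reference level of 0 to 1 courses would be nearly empty if women have at least 3 treated episodes.
3. **Antibiotic class by ATC group.**

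Estimate weights separately for each exposure, using a multi-level model where there are more than two levels. Align the wording of the Objective, Secondary End Points, Statistical Analysis and Discussion.

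No new data are needed: the Variables section already lists ATC-coded prescriptions with pharmacy invoice data. The cost is more analysis work and some loss of precision in each category.

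### Counting each patient only under the worst outcome conflicts with a separate risk ratio for each outcome, and the per-UTI primary end point of WP 2 does not match the per-individual model

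*Protocol article*

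**What the plan says.** For WP 2, the Statistical Analysis section first builds one severity variable from mortality and hospitalization, with pneumonia added for COVID-19 cases. It then turns to the weighted analysis: "For the primary outcome, marginal structural models will be fitted to estimate causal effects by correcting for confounders". The quantity to be estimated is the "risk ratio and confidence intervals for the prevalence of each outcome among individuals exposed to antibiotics", compared with individuals not exposed.

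The counting rule comes next. For relating earlier antibiotic use to the several outcomes, the article states that "patients will only be counted once and assigned to the worst outcome". The one ranking that it supplies stands in a parenthesis to that rule and reads "with the severity of COVID-19 ranked in decreasing order as death, hospitalization, and pneumonia". No order is given among pyelonephritis, sepsis, pneumonia and COVID-19 as complications.

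The Primary End Points section lists for WP 2 "the percentage hospitalization rate and the proportion of UTIs with complications (ie, pyelonephritis, sepsis, pneumonia, and COVID-19"). The second of these is a proportion of episodes. Items 6 and 7 of the Secondary End Points instead give percentages in two cohorts of women.

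The Discussion refers to "the use of suppressive antibiotic therapy as a prophylaxis in cases of recurrent UTI", and the study asks whether women so treated "have a higher incidence and severity of potentially serious future infections".

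**The concern.** A separate ratio for "confidence intervals for the prevalence of each outcome" needs every woman who had that outcome in the numerator, whatever else happened to her. The counting rule removes her from an outcome once she has a worse one. If exposure changes how often a milder event is accompanied by a worse one, cases are removed at different rates in the two groups, and the milder outcome's ratio no longer measures its occurrence. Greater severity under exposure is exactly what the study sets out to test. The rule would therefore pull the milder ratios down in the situation that the study is looking for.

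The unit of the primary end point is a second problem. The model compares individuals, while the end point divides by UTIs. Suppressive therapy is given to prevent UTIs, so the number of UTIs after exposure starts can be a result of exposure. Weights built from sociodemographic and clinical confounders do not repair a denominator that exposure itself has changed.

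**Working it through.** The article gives no event rates, overlap between outcomes, UTIs per woman or target risk ratio, so there is no planned figure to reproduce. The shares and reductions below are assumptions, shown as ranges.

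**1. Worst-outcome counting**

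Let p1 and p0 be the risks of any occurrence of a milder outcome in exposed and unexposed women. Let d1 and d0 be the shares of those cases who also have a worse-ranked outcome. The counted risks are p1(1−d1) and p0(1−d0), so

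counted RR = (p1/p0) × (1−d1)/(1−d0).

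Hospitalization with death ranked above it, true RR 1.20:

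| d0 | d1 | Counted RR | RR for hospitalization followed by death, 1.20 × d1/d0 |
|---|---|---|---|
| 10% | 10% | 1.20 × 0.90/0.90 = 1.20 | 1.2 |
| 10% | 15% | 1.20 × 0.85/0.90 = 1.13 | 1.8 |
| 10% | 20% | 1.20 × 0.80/0.90 = 1.07 | 2.4 |
| 10% | 30% | 1.20 × 0.70/0.90 = 0.93 | 3.6 |

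COVID-19 pneumonia with hospitalization and death ranked above it, true RR 1.20:

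- 30% vs 40%: 1.20 × 0.60/0.70 = 1.03
- 30% vs 50%: 1.20 × 0.50/0.70 = 0.86

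The factor is 1 only when d1 = d0 and is below 1 whenever d1 > d0. The top-ranked outcome has nothing above it, so its ratio does not change.

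**2. Where the rule reaches**

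- Narrow reading (COVID-19 severity only): the affected ratios are COVID-19 hospitalization and COVID-19 pneumonia, if each is estimated separately.
- Broad reading (the sentence speaks of the different outcomes): pyelonephritis, sepsis and pneumonia are also affected, but the article gives no order for them, so the rule cannot be applied as it stands.

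**3. Unit of the primary end point**

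Let f be the proportional reduction in UTIs per woman caused by exposure. Then

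per-UTI RR = per-woman RR / (1−f).

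- Per-woman RR 1.0, f = 25%: 1.0/0.75 = 1.33
- Per-woman RR 1.0, f = 50%: 1.0/0.50 = 2.0
- Per-woman RR 0.7, f = 25%: 0.7/0.75 = 0.93
- Per-woman RR 0.7, f = 50%: 0.7/0.50 = 1.4

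The fall in UTIs is inferred from the prophylactic purpose of suppressive therapy; the article gives no size for it. Item 7 of the Secondary End Points also places women with multiple antibiotic regimens in the exposed cohort. They may well have more UTIs than the comparator. In that case f is negative and the per-UTI ratio falls below the per-woman ratio.

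**The case against.** The strongest reply is that the rule only describes how the severity variable is coded. The ranking in parentheses names COVID-19 and uses the same three components as that variable, and worst-category assignment is a sound way to code a single severity scale. This reading is available, and nothing is wrong with the rule in that use. It does not settle the matter. The sentence refers to the different outcomes, and it follows directly on a plan for a risk ratio for each one. Even within COVID-19, separate ratios for hospitalization and pneumonia would be distorted.

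A reader might infer that every milder outcome is certainly biased. The article does not support that. Hospitalization is ranked above pneumonia only within COVID-19, nothing is ranked for pyelonephritis or sepsis, and the distortion is zero when d1 = d0. An order for the other complications could also stand in a fuller document; its absence here is not the fault. The fault is that the stated rule and the stated estimand cannot both hold.

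A reader might also infer that the plan will give results of the wrong sign. That is not shown. In the hospitalization example, the ratio crosses 1 only when the share with a worse outcome triples from 10% to 30%; smaller shifts only attenuate it.

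Finally, the two problems do not combine in one analysis. If each patient is counted once in a per-individual model, the per-UTI inflation does not arise there. What stands on that side is the mismatch between the end point and the model, and what would follow if the end point were analysed as it is worded. The direction of that effect is not fixed by the article.

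**Conclusion.** The point holds in a conditional form. Where worst-outcome assignment is used for separate risk ratios, which covers at least COVID-19 hospitalization and pneumonia, each milder ratio is multiplied by (1−d1)/(1−d0). If exposure raises severity, the result is too low: a true 1.20 is reported as 1.13 to 0.93 for assumed shares of 10% against 15% to 30%. The top-ranked outcome is safe, and so is any outcome for which exposure leaves the share with a worse event unchanged.

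Separately, the WP 2 primary end point per UTI disagrees with the per-individual model. This is a conflict between two statements, not a demonstrated bias in the planned risk ratio. If the per-UTI version were analysed, a per-woman ratio of 1.0 would appear as 1.33 to 2.0 for an assumed 25% to 50% reduction in UTIs, and could move the other way for women with multiple regimens. Both matters bear on the main WP 2 comparison and should be settled before the analysis.

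**What to change.** 1. Analyse hospitalization, pyelonephritis, sepsis, pneumonia, COVID-19 and death each as any occurrence (yes or no) per woman, regardless of her other outcomes.
2. State that worst-outcome assignment applies only to the single COVID-19 severity variable.
3. Restate the WP 2 primary end point per woman, or per person-time, so that it matches the model.

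The cost is a change of wording and a recoding of the same data. The outcomes will then overlap, so their counts will not add up to the number of women affected; the report should say so.
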